## Abstract

**Background:**

Asthma is one of the major chronic health problems in children in the Netherlands. The Pelican is a paediatric asthma-related quality of life instrument for children with asthma from 6–11 years old, which is suitable for clinical practice in primary and specialized care. Based on this instrument, we developed a self-management treatment to improve asthma-related quality of life. The Pelican intervention will be investigated in different health care settings. Results of intervention studies are often extrapolated to other health care settings than originally investigated. Because of differences in organization, disease severity, patient characteristics and care provision between health care settings, extrapolating research results could lead to unnecessary health costs without the desired health care achievements. Therefore, interventions have to be investigated in different health care settings when possible. This study is an example of an intervention study in different health care settings. In this article, we will present the study protocol of the Pelican study in primary and specialized care.

**Method/design:**

This study consists of two randomized controlled trials to assess the effectiveness of the Pelican intervention in primary and specialized care. The trial in primary care is a multilevel design with 170 children with asthma in 16 general practices. All children in one general practices are allocated to the same treatment group. The trial in specialized care is a multicentre trial with 100 children with asthma. Children in one outpatient clinic are randomly allocated to the intervention or usual care group. In both trials, children will visit the care provider four times during a follow-up of nine months. This study is registered and ethically approved.

**Discussion:**

This article describes the study protocol of the Pelican study in different health care settings. If the Pelican intervention proves to be effective and efficient, implementation in primary and specialized care for paediatric asthma in the Netherlands will be recommended.

**Trial registration:**

This study is registered by clinicaltrial.gov (NCT01109745)

## Background

Asthma [1] is the most common chronic disease in childhood in the Netherlands. Its prevalence ranges from 3% in children aged 5–9 years to 3.7% in children aged 10–14 years [2,3]. Although the prevalence is leveling off [4], asthma remains a significant burden for the child, family and the society at large [5]. In the Netherlands, children with intermittent and mild asthma are usually treated by a family physician, while patients with more severe or uncontrolled asthma are treated by specialized paediatric care [6]. This implies that children with asthma treated in primary and specialized care may differ in features like disease severity and complexity, level of symptom control, functional status and co-morbidity [7]. Recent reports point to substantial room for improvement in the management of childhood asthma [8-11]. Poor adherence to therapy and inadequately treatment are two important reasons why asthma is uncontrolled [9]. Poor adherence has been associated with discrepancies between the perceived relevance of treatment goals between patients and their healthcare providers. Usual care for children with asthma focuses on reducing morbidity and mortality by maintaining optimal asthma control, while asthmatic children want to live a normal life with as few limitations from their asthma as possible [12]. Taking the child’s perception into account in the management of its asthma could result in achieving treatment goals of patients and providers and contribute to patient centered care. However, recent studies pointed out that input of children and their parents into asthma management is only taken into account by health care providers during a minority (6 to 10%) of medical visits [13].

One of the important treatment outcomes showing a patient’s perspective is health related quality of life (HRQL). HRQL is a complex of all aspects of an individual’s subjective experience that relate to health, disease, disability and impairment, which is usually measured in physical, emotional, cognitive and social dimensions [14-17]. A HRQL questionnaire adds significant information about the functional impairments of a patient to clinical and physiological characteristics. Previous studies have shown that the most important HRQL components for children are consequences of asthma on peer relationships, dependence on medication, shortness of breath, cough, limitations in activities and limitations due to tobacco smoke exposure [18,19].

We have previously developed a child friendly web based tool to assess asthma-related quality of life in paediatric asthma patients, using the so-called ‘Pelican instrument’. In this paper, we describe the rationale for, and the designs of two randomized controlled trials (RCTs) that are based on the implementation of the Pelican instrument. In these trials the effectiveness of its implementation will be evaluated in both primary and specialized care setting in the Netherlands. Both trials are optimally adjusted in methodological design to meet the needs of the concerned care setting. Because of the known differences in healthcare organization and patient characteristics, it is important to establish possible effects of the treatment in both healthcare settings separately. In the past, results from specialized care studies have often been extrapolated into primary care, and vice versa [20,21]. Knowing that several important differences exist between these care setting, it is likely that this might lead to ineffective, unnecessary or expensive health care without the desired health achievements. Therefore, it is crucial to evaluate such interventions in primary as well as in specialized care.

### Hypothesis

The primary hypothesis of the Pelican study is that a self management treatment based on HRQL information (Pelican instrument) is able to improve HRQL on the PAQLQ-S (> 0.5 points) in children with asthma from 6–11 years old in primary and specialized care with a proportional difference in favour of intervention relative to usual care of 25% of children. Furthermore, it is also hypothesized that the instrument could improve asthma control and satisfaction with care of parents.

### Research questions

#### The primary research question

– Is the Pelican intervention in primary and specialized health care effective in improving HRQL of children with asthma?

#### The secondary research questions

– Is the Pelican intervention in primary and specialized health care effective in improving HRQL of the parents of children with asthma?

– Is the Pelican intervention in primary and specialized health care effective in improving asthma control of children with asthma?

– Does the Pelican intervention improve patient-doctor relationship and satisfaction with delivered care in primary and specialized health care?

– Is the Pelican instrument able to detect and improve psychosocial problems?

– Is the Pelican intervention user friendly in regular medical care and cost-effective in a primary and specialized care setting?

## Methods/design

### Study design

This study consists of two RCTs: one in primary care and one in specialized care. Because the study design, sample size calculation and treatment allocation differ between the trials, these aspects are described separately. All other aspects apply to both trials.

170 participants in primary care will be recruited from 16 general practices in the Netherlands. The primary care study is a multicentre parallel group study with a hierarchical or nested design. This means that all participating patients within a general practices will be allocated to the same treatment group (usual care or intervention group). During visits the usual care group receives care of the GP according NHG (Dutch GP Association) guidelines [22]. Besides usual care, the intervention group will receive recommendations based on the Pelican outcome by a practice nurse as well.

The most optimal study design for intervention studies is a multilevel design to avoid contamination between usual care and the intervention, which is applied in the primary care trial. There are, however, not enough outpatient clinics in the Netherlands to be able to use a multilevel design in specialized care. This means that specialized nurses provide care for both patients of the intervention and those of the usual care group. 100 participants in specialized care will be recruited in 5 outpatient clinics in the Netherlands. The usual care group receives care according to NVK (Dutch Association of paediatric) guidelines of paediatric asthma in the Netherlands of a care provider (e.g. paediatrician or nurse) [23]. The intervention group receives an intervention with the Pelican outcome by an asthma nurse complementary to usual care.

### Sample size calculation

A multilevel power calculation was performed for the trial in primary care based on the percentage of children with an improvement of 0.5 points on the PAQLQ instrument score (Δ0.5 is the minimum clinically important difference (MCID) for the PAQLQ) [14,24]. We consider a proportional difference in favour of intervention relative to usual care of 25% of children with a MCID to be clinically relevant. Based on the assumptions ICC = 0.04, α = 0.05, 1-β = 0.80, 20% of usual care group with a 0.5 points increase in PAQLQ score, and dropout rate of 15%, a total of 170 children with asthma needs to be included from 16 GPs.

A power calculation was performed for the trial in specialized care based on the percentage of children with an improvement of 0.5 points on the PAQLQ instrument score. We consider a proportional difference in favour of intervention relative to usual care of 25% of children with a MCID to be clinically relevant. Based on the assumptions α = 0.05, 1-β = 0.80, 10% of usual care group with a 0.5 points increase in PAQLQ score, and dropout rate = 15%, a total of 100 children with asthma needs to be included.

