### Randomisation: treatment allocation

Enrolment of participants will be performed by the general practices or outpatient clinics. Participants can be allocated to the usual care or intervention group. In both trials, the minimization technique will be used to allocate participants to treatment. Minimisation is an advanced randomisation technique as described by Pocock [26,27]. The balance between both groups will be kept with consideration of prognostic factors (categorical variables) as described below with a computer program called Minim.

In the primary care trial general practices will be allocated balanced on the following prognostic factors: 1) number of potential participants for study within GP (<18 or ≥18 patients with the diagnosis asthma between 6–11 years old) and 2) usual asthma care (absence of structured asthma care, structured asthma care for adults or structured asthma care for children).

In the specialized care trial the minimisation technique will be used to force treatment allocation of individual participants with consideration of the prognostic factors age (6–8 years old and 9–11 years old) and level of asthma control (ACQ score <1 and ACQ score ≥ 1).

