### Data analysis

The primary analysis is an intention-to-treat analysis, however both explanatory and intention-to-treat analyses will be performed. The effect of the Pelican in primary care will be analysed using multi-level analyses techniques. The effect of the Pelican in specialized care will be assessed using multivariate regression models. A correction for baseline value of the outcome of interest (e.g., HRQL, asthma control) will be added to the model.

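### Primary-care trial: 170 children from 16 practices gives the stated 80% power only with a normal critical value; on about 14 degrees of freedom the same inputs give about 74–77%

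*Protocol article*

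**What the plan says.** In the protocol article, Sample size calculation, the primary-care calculation uses "Based on the assumptions ICC = 0.04, α = 0.05, 1-β = 0.80, 20% of usual care group with a 0.5 points increase in PAQLQ score". The target effect is given as: "We consider a proportional difference in favour of intervention relative to usual care of 25% of children with a MCID to be clinically relevant". Allowing for 15% dropout, the conclusion is that "a total of 170 children with asthma needs to be included from 16 GPs". The calculation mentions neither a small-sample allowance for the number of practices nor variation in practice size.

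Study design states that all participating children in a practice receive the same treatment, so the practice is the unit of allocation. Randomisation: treatment allocation lists "number of potential participants for study within GP", split at 18, as a minimisation factor. Data analysis says "The effect of the Pelican in primary care will be analysed using multi-level analyses techniques", with correction for the baseline value of the outcome. It names no test statistic, reference distribution or degrees-of-freedom method.

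**The concern.** When whole practices are allocated, the error term for the treatment effect comes from variation between practices. The information on that term is set by the number of practices, not the number of children. A design effect enlarges the variance correctly, but it does not allow for that variance being estimated from only 16 units. A test that keeps its 5% level must therefore use a t distribution on about 14 degrees of freedom, and its power is below what 1.96 implies. Variation in practice size raises the design effect and lowers power further.

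At stake is the type II risk stated for this trial. The article wants a separate answer for each care setting, so a null result in primary care will be read against the claimed 80%.

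**Working it through.** **Inputs from the article.** Usual-care response 0.20; ICC 0.04; alpha 0.05; power 0.80; dropout 15%; 170 children; 16 practices.

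**Assumptions.**
- The test is two-sided.
- There are 8 practices per arm.
- The 25% difference is absolute, so 0.20 versus 0.45. Read as relative (20% versus 25%), it would need 1,094 per arm before clustering, which does not fit 170.

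**Step 1: reproduce 170.**
- Mean proportion = (0.20 + 0.45)/2 = 0.325.
- n per arm = [1.96 × √(2 × 0.325 × 0.675) + 0.842 × √(0.20 × 0.80 + 0.45 × 0.55)]² / 0.25² = 53.9, so 54 per arm and 108 in total.
- Analysed children = 170 × 0.85 = 144.5, or 144.5/16 = 9.03 per practice.
- Design effect = 1 + (9.03 − 1) × 0.04 = 1.321.
- Total = 108 × 1.321/0.85 = 168, in line with 170. With a continuity correction the total would be 193–203, so none was used.

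**Step 2: power with 1.96, equal sizes.**
- Effective n per arm = 72.25/1.321 = 54.7.
- Standard error = √(2 × 0.325 × 0.675/54.7) = 0.0896 pooled, or √(0.4075/54.7) = 0.0863 unpooled.
- Power = 80.6% (pooled) or 82.5% (unpooled). The stated 80% is met, with little margin.

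**Step 3: same inputs on 14 degrees of freedom.**
- Degrees of freedom = 16 − 2 = 14; two-sided 5% critical value 2.145.
- Noncentrality = 0.25/0.0896 = 2.79 (pooled) or 0.25/0.0863 = 2.90 (unpooled).
- Noncentral t power = 73.8% (pooled) or 76.8% (unpooled). Using the pooled error for the critical value and the unpooled error for the alternative gives 74.4%.
- Simulated multilevel models tested on 14 degrees of freedom agree: 74.8% (linear) and 75.6% (logistic).

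**Step 4: unequal practice sizes.** The article gives no coefficient of variation (CV), so a range is shown. Design effect = 1 + [(1 + CV²) × 9.03 − 1] × 0.04, which is 1.321 at CV 0, 1.354 at 0.3 and 1.412 at 0.5. The pooled column uses the pooled error for the critical value and the unpooled error for the alternative.

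| CV (assumed) | Power with 1.96, pooled / unpooled | Power on 14 df, pooled / unpooled |
|---|---|---|
| 0 | 80.6% / 82.5% | 74.4% / 76.8% |
| 0.3 | 79.6% / 81.6% | 73.4% / 75.8% |
| 0.5 | 77.9% / 80.0% | 71.6% / 74.1% |

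With the pooled error throughout, the 14-df figure at CV 0.5 is 70.9%. Simulation at CV 0.5 gave 71.5% (linear) and 73.2% (logistic).

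**Step 5: where the loss arises.** At equal sizes, moving from 1.96 to 2.145 costs about 6 points (80.6% to 74.4%; 82.5% to 76.8%). Going from CV 0 to 0.5 costs about 3 (74.4% to 71.6%; 76.8% to 74.1%). For scale, 80% power on the t basis at about 9 analysed children per practice (pooled) needs 18 practices, about 191 enrolled, with equal sizes (80.1%).

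**The case against.** The strongest reply is that the article made no slip: its inputs lead to its answer by a standard design-effect calculation, and what is asked for is a refinement. That is fair as to the sum. It does not rescue the power statement, because the article fixes both the number of practices and the 80%, and no later document can give 16 practices that power under a test that holds 5% on these inputs.

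Three stronger readings are tempting, and the documents support none of them.

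- **A reader might infer that the analysis will run at about 7% type I error.** P(|t| > 1.96) on 14 degrees of freedom is 7.0%, but that is the figure for a practice-level z test. Simulated multilevel Wald tests gave 5.2–7.2%, mostly near 6%. The article names no Wald test, and the degrees-of-freedom method is commonly left to the analysis plan. This is a conditional risk and not an error in the text.
- **A reader might infer that 80% needs equal practice sizes.** It does not: with 1.96, power is still 77.9–80.0% at CV 0.5.
- **A reader might take about 71% as the trial's power.** That figure needs an assumed CV. The minimisation factor splits potential participants, not enrolled children; it suggests that sizes vary but gives no spread.

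It can also be said that the actual analysis may be stronger than the responder comparison. The primary outcome is the PAQLQ-S, and the model corrects for baseline. If change scores were normal with equal SD, 20% versus 45% would be a shift of 0.842 − 0.126 = 0.716 SD, and power on 14 degrees of freedom would be about 94% (92% at CV 0.5). That rests on an analysis which the sample-size section does not use and on a distribution the article does not give. So baseline adjustment or a score analysis may recover power, but neither supports the stated 80%, which was derived for an unadjusted proportion.

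**Conclusion.** The point holds for the power statement. For the unadjusted responder comparison, 170 children from 16 practices gives about 74–77% power with equal practice sizes, not 80%, under a test that keeps the two-sided 5% level. The type II risk is therefore about 23–26% in place of the stated 20%. At an assumed CV of 0.5, power is about 71–74% and the type II risk about 26–29%.

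This rests on a two-sided test, an 8/8 split, an absolute difference of 25 points, 144.5 children analysed and the article's own ICC. An uneven split would not help. The shortfall is modest and does not threaten the design, but it affects how a null primary-care result should be read.

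**What to change.** Keep 170 children and 16 practices. In Sample size calculation, state that power for the unadjusted responder comparison is about 74–77% with equal practice sizes on 14 degrees of freedom, and give about 71–74% as a sensitivity figure at a CV of 0.5, labelled as an assumption. Add that baseline adjustment may raise power by an amount not quantified.

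In Data analysis, or in the analysis plan if it is not already there, specify a small-sample method for the primary-care treatment effect: Satterthwaite or Kenward-Roger degrees of freedom, or a practice-level t test on 14. The restated power and the 5% level then describe the same test.

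The cost is two or three sentences and a less favourable power figure; no further children or practices are needed.

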### Selection phase

In both trials children aged 6 to 12 years with asthma diagnosed by a physician will be recruited. Moreover, children must have used their asthma medication (i.e., bronchodilators and / or inhaled corticosteroids) for at least six weeks during the previous year to confirm ‘active asthma’. Exclusion criteria for these studies are: 1) a comorbide condition that significantly influences the HRQL, 2) not being able to attend a regular school class and 3) insufficient skill of Dutch language.

Parents of children are informed about the study by verbal explanation and an information brochure. For children, age-adjusted study information is provided on the website of the study. Written informed consent of both official caregivers will be obtained to ensure voluntary and anonymous participation. In accordance with the guidelines on scientific research with underage individuals, children may be withdrawn from the study at any time if they object [25].

### Randomisation: treatment allocation

Enrolment of participants will be performed by the general practices or outpatient clinics. Participants can be allocated to the usual care or intervention group. In both trials, the minimization technique will be used to allocate participants to treatment. Minimisation is an advanced randomisation technique as described by Pocock [26,27]. The balance between both groups will be kept with consideration of prognostic factors (categorical variables) as described below with a computer program called Minim.

In the primary care trial general practices will be allocated balanced on the following prognostic factors: 1) number of potential participants for study within GP (<18 or ≥18 patients with the diagnosis asthma between 6–11 years old) and 2) usual asthma care (absence of structured asthma care, structured asthma care for adults or structured asthma care for children).

In the specialized care trial the minimisation technique will be used to force treatment allocation of individual participants with consideration of the prognostic factors age (6–8 years old and 9–11 years old) and level of asthma control (ACQ score <1 and ACQ score ≥ 1).

### Pelican instrument

The paediatric Electronic quality of Life Instrument for Asthmatic children in the Netherlands or Pelican is a web-based asthma-related quality of life questionnaire that is presented as a web-based computer game. It is effortless to complete, easy to understand (questions are read aloud) and full of attractive sounds and pictures. While playing the game, the child answers questions about his or her experience of asthma. Item selection for the Pelican was based on children’s personal perspectives that were obtained using focus groups [18]. Items are concrete aspects of day-to-day life with asthma what makes them an easy starting point for treatment and are scored in burden experience on a 5-point Likert scale ranging from ‘no burden at all’ (0 points) to ‘very high burden’ (5 points). Scores are visually supported by emoticons. Besides overall quality of life, the instrument has the ability to priorities issues of asthma bothering the patient most.

### Intervention

The intervention is a self-management treatment based on the patient’s reply to the Pelican questionnaire. Treatment is provided by a specialized nurse with the objective to improve the patient’s asthma-related quality of life. The nurse is trained during a 2-hour meeting in this intervention with theoretic background, video instructions and role playing exercises. Supplementary to the training, a minimum of five evaluation moments are included during the trial.

The child fills out the Pelican before the scheduled visit and the outcome is forwarded to the nurse. The intervention is based on the theory of behaviour change and shared decision making [28]. The health care provider supports the parent and child to explore their needs and treatment goals (according SMART principles [29]) and think about solutions for disease related problems and challenges. Together, the parent, child and nurse work on a treatment plan to improve disease management resulting in better disease outcomes. The treatment plan is a mutual agreement that is specific, acceptable and realistic. During the next visit, the nurse will evaluate the effectiveness of the treatment plan: why was it successful or unsuccessful to achieve treatment goals. If not successful, the care provider will explore the causes (lack of knowledge/skills, motivational, practical or social barriers) and evaluate whether they can be resolved.

